### Primary outcome

The two groups will be compared using inferential statistics for their mean change in the primary variable (Foot functional index and modified star excursion test) between baseline and six weeks. For research participants, random effects will be generalised, treatment group and visit count will be taken into consideration while analysing fixed effects. At the conclusion of the intervention, the effect size over the mean change difference on the primary variable will be assessed and the matching 95% confidence interval (CI) given.

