### Outcome measures

**Primary outcomes**

1.

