**Foot Function Index (FFI)**
the Foot Function Index (FFI) was designed to analyze the effect of foot abnormalities on performance in terms of pain, functional limitations, and activity restriction. The internal consistency was between 0.96 and 0.7.
^
15
^
2.

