**The Modified Star Excursion Balance Test (mSEBT)**
The SEBT (Star Excursion Balance Test) is a multi-dimensional test that includes power, mobility, and postural control. This is a dynamic balancing measurement that poses a substantial challenge to players and healthy and active adults. The evaluation is used to measure functional ability as well as to screen for inadequacies in dynamic balance caused by musculoskeletal disorder. coefficients of variation ranging from 2.0 to 2.9 percent, the mSEBT has been shown to be a valid indicator of dynamic balance.
^
17
^

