### Sample size calculation

Sample size calculation resulted at 5% level of significance considering Z (1-α) value = 1.96 and (1- β) at power of 80% = 0.84 measuring the expected mean difference for superiority (effect side) of (δ) = 2.602 and standard deviation (σ) = 3.24

Formula Using Mean difference

$$n1=n2=2\frac{{\left(Z_{\alpha }+Z_{\beta }\right)}^{2}\sigma^{2}}{{\left(\delta \right)}^{2}}$$

Primary variable – (Foot Functional Index)

Mean. (Pre) result on Foot Functional Index for foot core exercises with conventional physiotherapy = 72.68

Mean. (Post)- result on Foot Functional Index for foot core exercises with conventional physiotherapy = 59.67 ± 10.69

Difference (mean ± SD) = 13.01 ± 3.24 (As per reference article)

Clinically relevant superiority = 20% = (13.01 *20)/100 = 2.602

$$\text{N1}=2^{*}\left[{\left(1.96+0.84\right)}^{2}\;{\left(3.24\right)}^{2}\right]/{\left(2.602\right)}^{2}=25$$

Minimum samples required = 25 per group

Considering 30% drop out = 8

Total sample size required = 33 per group

Assumptions

$$Z_{\alpha }=1.96$$

α=TypeIerrorat5%

$$Z_{\beta }=0.84\;\left(1-\beta \right)=\text{Power}\;\mathrm{at}\;80\%$$

σ=std.dev

Ref Article: - Jadhav and Gurudut.
^
20
^

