### Primary endpoint

To predict the difference in effect size between the active and control groups, secondary outcomes (the visual analogue scale and the weight bearing lunge test) will be examined in accordance with the mixed model effect. If the data is distributed normally, the T-test (unpaired) will be performed to determine whether there is a significant difference between the means of the two groups. The data will be transformed into a normal distribution for non-normal distributions using mathematical techniques. If the primary variable's data still exhibits a non-normal distribution, an alternative non-parametric test will be used (Chi square, Mann Whitney, Wilcoxon test).

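### The primary outcome is FFI alone in the sample size section but FFI and mSEBT elsewhere, with no success rule, so the stated 5% and 80% do not both hold for two unordered primaries

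*Protocol article*

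**What the plan says.** All references are to the protocol article.

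- **Outcome measures.** The plural heading "Primary outcomes" has two entries: the FFI, and "The Modified Star Excursion Balance Test (mSEBT)". VAS and WBLT follow as secondary.
- **Sample size calculation.** One variable is named: "Primary variable – (Foot Functional Index)". The only significance level in the article is here: "Sample size calculation resulted at 5% level of significance considering Z (1-α) value = 1.96". With 80% power, a difference of 2.602 and an SD of 3.24, the result is 25 per group, raised to 33 for dropout. Nothing is calculated for mSEBT.
- **Primary outcome** (analysis). The groups are compared on "mean change in the primary variable (Foot functional index and modified star excursion test) between baseline and six weeks", with an effect size and "the matching 95% confidence interval (CI) given". The section gives no either, both or ordered rule.
- **Primary endpoint** (analysis). Despite the heading, the text says "secondary outcomes (the visual analogue scale and the weight bearing lunge test) will be examined in accordance with the mixed model effect". Its last sentence then sets the non-parametric fallback for the primary variable.

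**The concern.** The trial is declared a superiority trial, so a reader must be able to tell which comparison carries the claim. The sample size section answers FFI. The outcome list and the primary analysis answer FFI and mSEBT. The heading *Primary endpoint* adds confusion, because the outcomes under it are not primary by the protocol's own account.

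Two things are at stake. First, if the choice is left until results are known, whichever of FFI or mSEBT looks better can become the headline. Second, the design figures of 5% error and 80% power were derived for a single FFI test. They carry over to a two-primary trial only under some decision rules, and the article states none.

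**Working it through.** **Inputs from the protocol (Sample size calculation):** two-sided α = 0.05 (z = 1.96), power 80% (z = 0.84), δ = 2.602, σ = 3.24, equal groups.

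**Assumptions, not in the protocol:** the correlation between the FFI and mSEBT test statistics (range 0 to 0.9 shown) and, for joint power only, that mSEBT has the same standardised effect as FFI.

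**1. The plan's own figure.**
n = 2 × (1.96 + 0.84)² × 3.24² / 2.602² = 2 × 7.84 × 10.4976 / 6.7704 = 24.3, rounded up to 25 per group. This reproduces. Adding 30% (25 × 1.3 = 32.5) gives the stated 33.

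**2. FFI as the only test at 5%.**
Standardised difference at 25 per group: 2.602 / (3.24 × √(2/25)) = 2.839.
Power = Φ(2.839 − 1.960) = Φ(0.879) = 81.0%.
The stated 5% and 80% hold.

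**3. Two primaries, either may win, each tested at 5%.**
If independent: 1 − 0.95² = 9.75% (Bonferroni bound 10%).
If correlated: 1 − P(|Z₁| < 1.96 and |Z₂| < 1.96) under a bivariate normal.

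| Assumed correlation | Family-wise error |
|---|---|
| 0 | 9.75% |
| 0.3 | 9.5% |
| 0.5 | 9.1% |
| 0.7 | 8.4% |
| 0.9 | 7.0% |

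The stated 5% is lost.

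**4. Two primaries, alpha split 2.5% each.**
Family-wise error if independent: 1 − 0.975² = 4.94%.
FFI power at 25 per group: Φ(2.839 − 2.241) = Φ(0.598) = 72.5%.
Restoring 80% for FFI needs 30 per group before dropout, or 39 with the plan's own dropout allowance (30 × 1.3).
The stated 80% is lost.

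**5. Two primaries, both must win, each at 5%.**
Error does not exceed 5%. Joint power at 25 per group, with equal standardised effects:

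| Assumed correlation | Joint power |
|---|---|
| 0 | 0.810² = 65.7% |
| 0.3 | 68.1% |
| 0.5 | 70.2% |
| 0.7 | 72.6% |
| 0.9 | 76.2% |

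The stated 80% is lost.

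**6. Fixed sequence, FFI first.**
FFI is tested at the full 5%, and mSEBT only if FFI is significant. FFI keeps its 81.0% power at 25 per group, and family-wise error stays within 5%.

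The published sample size therefore supports FFI as the sole primary, or as the first of an ordered pair. The *Primary outcome* section states neither.

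**The case against.** **A multiplicity rule may exist elsewhere.** This is a condensed article. An alpha split, a testing order or a both-required rule commonly sits in a full protocol or analysis plan that is not shown. That is fair, and the missing rule alone would not be a finding. But an unseen rule would not remove the mismatch between the sample size section and the outcome list, or the wrong heading.

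**Sizing on one of two primaries is not by itself an error.** That also stands. It is coherent if FFI is sole or first; the article does not say so.

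**The wording may imply that both must succeed.** The analysis section uses a singular noun and joins the two instruments with *and*. If both are required there is no false-positive inflation, and the cost falls on power.

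**Full retention would soften the power loss.** If all 33 per group were analysed, FFI power at 2.5% would be 84.6%. The plan, however, makes its power claim at 25 per group and treats the other 8 as expected losses.

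Three stronger readings are tempting, and the text does not support them:

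- *Three rival definitions of the primary outcome.* There are two. The *Primary endpoint* section calls VAS and WBLT secondary, as the outcome list does, so its heading is simply wrong.
- *Two primaries each tested at 5%, so the false-positive risk nearly doubles.* The 5% level is stated once, for the FFI calculation. Applying it to each outcome is an inference from that single level and the unadjusted 95% interval, and the near-doubling also needs an either-may-win rule that is not stated.
- *Four endpoints each able to carry the claim.* Nothing in the text makes VAS or WBLT primary.

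**Conclusion.** The point holds as an internal inconsistency. The trial is sized on FFI as its one primary variable but lists and analyses FFI and mSEBT as primary, without saying how the two combine. None of the unordered two-primary rules examined keeps both stated design figures at 25 per group:

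- either may win: error of 7.0% to 9.75%;
- alpha split: FFI power of 72.5%;
- both required: joint power of about 66% to 76%.

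The error range rests on assumed correlations. The joint power rests also on an assumed mSEBT effect equal to FFI's, because the article gives neither quantity. All the power figures take the protocol's own difference and SD as given. The inconsistency itself depends on none of these assumptions. It should be settled before recruitment, because a headline outcome chosen after the data are seen cannot be credibly called prespecified.

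**What to change.** 1. Name one primary endpoint throughout: the between-group difference in FFI change from baseline to six weeks. This is the quantity already in the *Primary outcome* analysis section, and it matches the sample size section.
2. Make mSEBT secondary, or test it at 5% only after FFI is significant at 5% (fixed sequence). Align the outcome list and the *Primary outcome* section.
3. If both are to stay co-primary, state the success rule (either with an alpha split, or both required) and restate the power. This needs an mSEBT effect and SD, which the article does not give.
4. Retitle the *Primary endpoint* section *Secondary outcomes*, and move its sentence on the primary variable's non-normal fallback into the *Primary outcome* section.

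**Cost.** With items 1, 2 and 4, only wording changes: no new data, no extra participants, and 25 per group before dropout still stands. The price is that mSEBT loses stand-alone primary status. Choosing item 3 with an alpha split would raise the FFI requirement to 30 per group before dropout. The *Study status* section says the trial has yet to start, so the change can be made before any data exist.

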### Primary endpoint

To predict the difference in effect size between the active and control groups, secondary outcomes (the visual analogue scale and the weight bearing lunge test) will be examined in accordance with the mixed model effect. If the data is distributed normally, the T-test (unpaired) will be performed to determine whether there is a significant difference between the means of the two groups. The data will be transformed into a normal distribution for non-normal distributions using mathematical techniques. If the primary variable's data still exhibits a non-normal distribution, an alternative non-parametric test will be used (Chi square, Mann Whitney, Wilcoxon test).

### Dissemination

To present the research findings at conferences, seminars, community forums etc.

### Study status

The study is yet to start.

## Discussion

The purpose of this study to analyse the efficacy of ankle pnf vs standard foot core exercises in enhancing functional capacities, enhancing dynamic balance, increasing joint mobility, and reducing discomfort in individuals who are suffering from plantar fasciitis. Poor foot posture can lead to structural abnormalities throughout the body because it places enormous strain on the lower extremity’s joints and muscles. If this abnormal pressure is not alleviated, it will continue to cause discomfort, fatigue, and musculoskeletal injury. When a person has plantar fasciitis, the fascia becomes inflamed because of excessive intense activity, which causes pain and discomfort when doing weight-bearing activities like walking. When engaging in weight-bearing activities, dynamic balance control can be impacted by pain.
^
21
^

Numerous studies demonstrate the impact on the reduction of pain, improve joint mobility and foot function, etc. According to Ranbhor
*et al.,* foam rolling and calf and plantar fascia stretching both aided with pain relief and joint motion. However, the outcome measure shows boosting effects in the foam rolling than the traditional stretching exercises.
^
22
^ According to Kaur and Koyal's study, stretching the Achilles tendon produced a significant improvement in the patient's outcome variables, but stretching the calves reduced discomfort and foot function deficit but did not have the same impact.
^
23
^ According to Kumar
*et al*., low dye taping combined with stretching of the plantar fascia and strengthening of the intrinsic muscles was an effective method for reducing pain and enhancing functional activities. Both groups showed a substantial improvement in all categories, however the people who had low dye taping saw a considerably superior overall improvement. Consequently, low dye tape is an effective intervention method for the treatment of plantar fasciitis patients.
^
24
^

By analysing the outcome, we will be evaluating the impact of foot core exercises and ankle pnf on dynamic balance and compare both the intervention in this study. Muscle strength in the fundamental body parts is crucial for maintaining balance. Accurate and efficient exercise of these muscles appears to be of utmost importance since they play a significant function secondary to that of the foot, as well as in relation to the complete kinematic chain.

### Ethical considerations

Institutional Ethics Committee of Datta Meghe Institute of Higher Education and Research (Deemed to be University) approved this study.

DMIHER (DU)/IEC/2023/804 is the reference number.

## Data Availability

Not applicable as this is a protocol. Zenodo: SPIRIT Checklist DOI:
10.5281/zenodo.7990088.
^
25
^ Data are available under the terms of the
Creative Commons Attribution 4.0 International license (CC-BY 4.0).
